### **Adverse Events**

The verbatim terms used in the CRF by investigators to identify adverse events will be coded using the Medical Dictionary for Regulatory Activities (MedDRA). All reported adverse events with onset during the treatment phase (ie, treatment-emergent adverse events, and adverse events that have worsened since baseline) will be included in the analysis. For each adverse event, the percentage of subjects who experience at least 1 occurrence of the given event will be summarized by treatment group.

Only adverse events as defined in Section 12.3.1, All Adverse Events, whether serious or non-serious, that occur between the first use of investigational product (telaprevir) and 30 days after administration of the last dose of telaprevir will be collected and summarized. Particular attention will be given to adverse events of special interest, eg, rash and anemia.

Summaries, listings, datasets, or subject narratives may be provided, as appropriate, for those subjects who die, who discontinue treatment due to an adverse event, or who experience a severe or a serious adverse event.

## **12. ADVERSE EVENT REPORTING**

Timely, accurate, and complete reporting and analysis of safety information from clinical studies are crucial for the protection of subjects, investigators, and the sponsor, and are mandated by regulatory agencies worldwide. The sponsor has established Standard Operating Procedures in conformity with regulatory requirements worldwide to ensure appropriate reporting of safety information; all clinical studies conducted by the sponsor or its affiliates will be conducted in accordance with those procedures.

### **12.1. Definitions**

#### **12.1.1. Adverse Event Definitions and Classifications**

##### **Adverse Event**

An adverse event is any untoward medical occurrence in a clinical study subject administered a medicinal (investigational or non-investigational) product. An adverse event does not necessarily have a causal relationship with the treatment. An adverse event can therefore be any unfavorable and unintended sign (including an abnormal finding), symptom, or disease temporally associated with the use of a medicinal (investigational or non-investigational) product, whether or not related to that medicinal (investigational or non-investigational) product. (Definition per ICH)

This includes any occurrence that is new in onset or aggravated in severity or frequency from the baseline condition, or abnormal results of diagnostic procedures, including laboratory test abnormalities.

Note: The sponsor collects adverse events starting with the first use of investigational product (refer to Section 12.3.1, All Adverse Events for time of last adverse event recording).

### **Serious Adverse Event**

A serious adverse event based on ICH is any untoward medical occurrence that at any dose:

- Results in death
- Is life-threatening  
(The subject was at risk of death at the time of the event. It does not refer to an event that hypothetically might have caused death if it were more severe.)
- Requires inpatient hospitalization or prolongation of existing hospitalization
- Results in persistent or significant disability/incapacity
- Is a congenital anomaly/birth defect
- Is a suspected transmission of any infectious agent via a medicinal product
- Medically Important\*

\*Medical and scientific judgment should be exercised in deciding whether expedited reporting is also appropriate in other situations, such as important medical events that may not be immediately life threatening or result in death or hospitalization but may jeopardize the subject or may require intervention to prevent one of the other outcomes listed in the definition above. These should usually be considered serious.

### **Unlisted (Unexpected) Adverse Event/Reference Safety Information**

An adverse event is considered unlisted if the nature or severity is not consistent with the applicable product reference safety information. For an investigational product, the expectedness of an adverse event will be determined by whether or not it is listed in the Investigator's Brochure. For non-sponsor medicinal products to be administered during this study (eg, combination therapy) with a marketing authorization, the expectedness of an adverse event will be determined by whether or not it is listed in the local prescribing information. Investigator's should follow standard practice for reporting unlisted adverse events to the marketing authorization holder for the standard-of-care therapy (ie, Peg-IFN-alfa, RBV) administered with telaprevir in this expanded access program.

### **Associated With the Use of the Drug**

An adverse event is considered associated with the use of the drug if the attribution is possibly related or related by the definitions listed in Section 12.1.2.

### **12.1.2. Attribution Definitions**

#### **Not Related**

An adverse event which is not related to the use of the drug.

#### **Unlikely Related**

An adverse event for which an alternative explanation is more likely, eg, concomitant drug(s) or concomitant disease(s), and/or the relationship in time suggests that a causal relationship is unlikely.

#### **Possibly Related**

An adverse event which might be due to the use of the drug. An alternative explanation, eg, concomitant drug(s) or concomitant disease(s), is inconclusive. The relationship in time is reasonable; therefore the causal relationship cannot be excluded.

#### **Related**

An adverse event which might be due to the use of the drug. The relationship in time is suggestive, eg, confirmed by dechallenge. An alternative explanation is less likely, eg, concomitant drug(s) or concomitant disease(s).

### **12.2. Special Reporting Situations**

Safety events of interest on a sponsor medicinal product (telaprevir) that may require expedited reporting and/or safety evaluation include, but are not limited to:

- Overdose of a sponsor medicinal product
- Suspected abuse/misuse of a sponsor medicinal product
- Inadvertent or accidental exposure to a sponsor medicinal product
- Medication error involving a sponsor product (with or without subject/patient exposure to the sponsor medicinal product, eg, name confusion)

Special reporting situations which occur between the first use of telaprevir and 30 days after administration of the last dose of telaprevir should be recorded in the CRF. Any special reporting situation that meets the criteria of a serious adverse event should be recorded on the serious adverse event page of the CRF.

#### **12.2.1. Severity Criteria**

Please refer to Section 9.3.1.1.1 (rash) and Attachment 3 (other adverse events).

### **12.3. Procedures**

#### **12.3.1. All Adverse Events**

All adverse events, as defined below, which occur between the first use of investigational product (telaprevir) and 30 days after administration of the last dose of telaprevir will be recorded in the CRF. Serious adverse events, including those spontaneously reported to the investigator more than 30 days after the last dose of investigational product (telaprevir), must be reported using the Serious Adverse Event Form. The sponsor will

evaluate any safety information that is spontaneously reported by an investigator beyond the time frame specified in the protocol.

The DAIDS criteria will be used to grade all adverse events except for rash which has protocol-specific definitions of severity grades provided in Section 9.3.1.1.1.

The following adverse events will be recorded in the CRF:

- Adverse events of special interest
  - All rash and anemia events, regardless of DAIDS grade or relationship to telaprevir
- The following which are considered at least possibly related to telaprevir by the investigator
  - All adverse events, including laboratory abnormalities, with DAIDS grade 2 (moderate) or higher
  - Other adverse events (ie, DAIDS grade 1 [mild]), including laboratory abnormalities, considered medically significant (eg, require medical intervention)
- All adverse events leading to discontinuation of telaprevir, regardless of DAIDS grade or relationship to telaprevir
- All serious adverse events, regardless of relationship to telaprevir
- Any pregnancy in female subjects or in female partners of male subjects; see Section 12.3.3
- Special reporting situations: overdose, suspected abuse/misuse, inadvertent or accidental exposure, or medication error of telaprevir; see Section 12.2
- Other adverse events will be recorded as per local regulations only

All adverse events, as defined above, must be recorded using medical terminology in the source document and the CRF. Whenever possible, diagnoses should be given when signs and symptoms are due to a common etiology (eg, cough, runny nose, sneezing, sore throat, and head congestion should be reported as “upper respiratory infection”). Investigators must record in the CRF their opinion concerning the relationship of the adverse event to study therapy. All measures required for adverse event management must be recorded in the source document and reported according to sponsor instructions.

The sponsor assumes responsibility for appropriate reporting of adverse events to the regulatory authorities. The sponsor will also report to the investigator all serious adverse events that are unlisted (unexpected) and associated with the use of the study drug (telaprevir). The investigator (or sponsor where required) must report these events to the appropriate Independent Ethics Committee/Institutional Review Board (IEC/IRB) that approved the protocol unless otherwise required and documented by the IEC/IRB.

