## **11. STATISTICAL METHODS**

### **11.1. Analysis Population**

The intent-to-treat analysis population will be defined as all enrolled subjects who received at least 1 dose of telaprevir. The intent-to-treat analysis population will be used for all statistical analyses, unless otherwise specified.

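### For non-serious adverse events outside rash, anemia and telaprevir discontinuation, the planned percentages can mix country-dependent recording with an all-treated denominator

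*Protocol*

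**What the plan says.** Section 12.3.1 introduces its list with "The following adverse events will be recorded in the CRF". The list has three tiers that matter here; the Synopsis (Safety Evaluations) repeats them.

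- **Recorded everywhere, whatever the attribution:** "All rash and anemia events, regardless of DAIDS grade or relationship to telaprevir", events that lead to stopping telaprevir, and serious adverse events. Section 12.3.2 takes hepatitis C related events out of the serious category unless they are fatal or attributed to telaprevir.
- **Recorded everywhere, but only if attributed:** "The following which are considered at least possibly related to telaprevir by the investigator". This covers events of grade 2 or higher and medically significant grade 1 events.
- **Everything else:** "Other adverse events will be recorded as per local regulations only".

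The text after the list requires all the events it defines to be entered in both the source document and the CRF.

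The Adverse Events part of Section 11.5 brings every reported event with treatment-phase onset into the analysis. It limits what is collected and summarised by reference to the same list: "Only adverse events as defined in Section 12.3.1, All Adverse Events, whether serious or non-serious". The summary measure is stated without qualification: "For each adverse event, the percentage of subjects who experience at least 1 occurrence of the given event will be summarized by treatment group". On the denominator, Section 11.1 says: "The intent-to-treat analysis population will be used for all statistical analyses, unless otherwise specified". That population is all enrolled subjects with at least one telaprevir dose. Section 3.1 describes the program as multinational.

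**The concern.** A percentage of subjects with an event needs one recording rule for everyone in the denominator. For a non-serious event that is not rash or anemia and does not stop telaprevir, the list gives two rules. Attributed events of sufficient grade count in all countries. Other occurrences of the same event count only where local regulations ask for them. The denominator is everyone in either case.

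If local rules differ, the tabulated figure is a mixture. It understates how often the event occurred, because some occurrences were never recorded. It overstates how often a telaprevir-attributed event occurred, because unattributed or mild occurrences from some countries are in the count. A change in enrolment by country would move the figure with no change in risk. A confidence interval put around it would reflect sampling error only.

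Collecting additional safety data is one of the program's two stated objectives (Section 2), so the meaning of these percentages matters even in a descriptive analysis.

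**Working it through.** **1. The plan's own precision figures.** Section 11.4 tabulates half-widths of 95% intervals. The formula is half-width = 1.96 × √(p(1 − p)/N). At N = 3,000:

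- p = 10%: 1.96 × √(0.10 × 0.90/3,000) = 1.07 points (plan: 1.1), giving 8.9% to 11.1% as the plan states.
- p = 20%: 1.96 × √(0.20 × 0.80/3,000) = 1.43 points (plan: 1.4).
- p = 30%: 1.96 × √(0.30 × 0.70/3,000) = 1.64 points (plan: 1.6).

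All 15 cells reproduce to one decimal. The table itself is correct.

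**2. What the table would show.** Let

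- P = true percentage of subjects with the event,
- c = share of affected subjects whose event meets a criterion that applies in every country,
- s = share of subjects in countries that require the remaining events to be recorded.

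Then recorded % = P × [c + (1 − c) × s], and the shortfall is P × (1 − c) × (1 − s). The documents give neither c nor s, so both are assumptions. P and c are taken as equal across countries.

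**3. Illustration at P = 20%.**

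| c | s = 0 | s = 0.25 | s = 0.5 | s = 0.75 | s = 1 |
|---|---|---|---|---|---|
| 0.25 | 5.0% | 8.75% | 12.5% | 16.25% | 20.0% |
| 0.5 | 10.0% | 12.5% | 15.0% | 17.5% | 20.0% |
| 0.9 | 18.0% | 18.5% | 19.0% | 19.5% | 20.0% |

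Example: c = 0.5, s = 0.25 gives 20 × (0.5 + 0.5 × 0.25) = 12.5%.

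The two ends of each row have a clear meaning. At s = 0 only the universal criteria count. At s = 1 the figure is the full incidence. Every value between is neither.

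**4. When it exceeds sampling error.** The shortfall is larger than the half-width at P when (1 − c)(1 − s) exceeds half-width/P. At N = 3,000 the thresholds are:

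- P = 10%: 1.07/10 = 0.107
- P = 20%: 1.43/20 = 0.072
- P = 30%: 1.64/30 = 0.055

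So at a true rate of 20%, about 7% of affected subjects going unrecorded is enough.

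**The case against.** The strongest reply has four parts.

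*Selective collection is disclosed.* The Hypothesis paragraph of Section 2 says only selected safety data are collected, and Section 11.5 calls the analyses descriptive. This stands for the attribution filter. On its own the filter defines a valid quantity, the percentage with a telaprevir-attributed event of sufficient grade, and needs only a label. It does not answer the third tier, where selection can differ by country inside one pooled figure.

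*The list's last item may be meant to send the remaining events outside the CRF.* Section 9.3 and the Time and Events Schedule footnotes restrict the CRF to protocol-defined events, so the wording is not free of ambiguity. But the item sits under the CRF heading, and the text that follows requires everything so defined to be entered there. The natural reading puts these events in the database.

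*Country differences are not documented.* This is correct. No section says which countries, if any, require the extra recording. If all or none do, the mixing disappears.

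*The analysis plan could set another denominator.* Section 11.1 allows it. But Section 11.5 positively includes all reported events, so excluding the locally recorded ones would depart from the protocol's text rather than fill a gap in it.

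A reader might go on to infer that country would emerge as a prognostic factor in the regressions, or that misleading intervals would accompany every event. The documents do not support either. Section 11.5 makes the regressions optional and does not name country, and Section 11.4 promises intervals only for selected events.

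**Conclusion.** The point holds for one class: non-serious adverse events other than rash, anemia and events leading to telaprevir discontinuation. As written, Sections 12.3.1, 11.5 and 11.1 allow a numerator whose completeness depends on country over a denominator of all treated subjects. The size is unknown because c and s are unknown. With P = 20% and c = 0.5 the recorded figure ranges over 10 points by country mix alone, about seven times the 1.43-point half-width (10/1.43 = 7.0). With c = 0.9 the range is 2 points.

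Two stronger readings should be resisted. The first is that all adverse event percentages are compromised. Rash, anemia, discontinuation events and serious events are recorded everywhere regardless of attribution, apart from the hepatitis C exclusion in Section 12.3.2. These include the events of special interest and the serious event used in the precision example. The second is that the table would show simply s × P, for example 20% × 40% = 8% for an event with 40% incidence. That requires c = 0, meaning that no affected subject's event meets a universal criterion. Section 11.5 tabulates each event as a whole, so attributed, serious and discontinuation cases count everywhere. At the same P and s, c = 0.5 gives 24% and c = 0.9 gives 36.8%.

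**What to change.** In Section 11.5, and in the analysis plan to match:

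- Restrict pooled percentages, and any confidence intervals, to the categories recorded in every country.
- List events recorded only under local regulations separately, or summarise them with only the subjects in the recording countries as denominator.
- Title the attribution-filtered tables as events the investigator considered possibly related or related to telaprevir, so that they are not read as overall incidence.
- Footnote the serious adverse event tables with the hepatitis C exclusion from Section 12.3.2.

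The cost is a wording change and one programmed flag built from the grade, relationship, seriousness and action-taken fields. The headline table will hold slightly fewer events. Data collection does not change.

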### **12.3.2. Serious Adverse Events**

All serious adverse events occurring during clinical studies must be reported to the appropriate sponsor contact person by investigational staff within 24 hours of their knowledge of the event.

Information regarding serious adverse events will be transmitted to the sponsor using the Serious Adverse Event Form, which must be completed and signed by a member of the investigational staff, and transmitted to the sponsor within 24 hours. The initial and follow-up reports of a serious adverse event should be made by facsimile (fax).

All serious adverse events that have not resolved by the end of the early access program, or that have not resolved upon discontinuation of the subject's participation in the early access program, must be followed until any of the following occurs:

- The event resolves
- The event stabilizes
- The event returns to baseline, if a baseline value/status is available
- The event can be attributed to agents other than the study drug or to factors unrelated to the conduct of the early access program
- It becomes unlikely that any additional information can be obtained (subject or health care practitioner refusal to provide additional information, lost to follow-up after demonstration of due diligence with follow-up efforts)

Suspected transmission of an infectious agent by a medicinal product will be reported as a serious adverse event. Any event requiring hospitalization (or prolongation of hospitalization) that occurs during the course of a subject's participation in this early access program must be reported as a serious adverse event, except hospitalizations for the following:

- Conditions which existed prior to the trial and which did not deteriorate during the trial
- Treatment or care of hepatitis C diseases unless fatal or considered to be related to telaprevir
- Investigational or elective procedures

Hepatitis C infection is characterized by a series of infections and neoplasms, which depending on the disease stage of the subject may constitute a life-threatening event. Reporting all such events as serious adverse events could divert attention from the serious adverse events that could be related to the study drug. Therefore for this early access

program the following occurrences will NOT be recorded or reported as serious adverse events:

- Any condition which occurred prior to the subject being enrolled in the early access program and did NOT worsen during the trial. These conditions should be recorded at the screening visit.
- Hepatitis C related events, unless fatal or judged to be associated with the use of telaprevir

The cause of death of a subject in a clinical study within 30 days of last dose of telaprevir, whether or not the event is expected or associated with the investigational agent, is considered a serious adverse event.

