#### **Liver Disease and Primary Hepatocellular Carcinoma due to HCV**

After human immunodeficiency virus (HIV), HCV has the second highest rate of morbidity and mortality amongst recently discovered infectious diseases. Hepatitis C virus is the most common infectious cause of chronic liver disease in Europe.

Chronic HCV infection causes hepatic inflammation, which typically progresses to varying degrees of hepatic fibrosis, including cirrhosis. Once cirrhosis is present, the patient is at risk for hepatic decompensation (ascites, variceal bleeding, portosystemic encephalopathy), development of primary hepatocellular carcinoma (HCC), need for liver

transplant, and death due to liver disease. It is estimated that 20% to 30% of patients with chronic hepatitis C progress to cirrhosis.

From prospective studies, more accurate data are available on the risk of hepatic decompensation, HCC, and survival rates once advanced hepatic fibrosis and cirrhosis are diagnosed. In subjects with clinically compensated cirrhosis, the cumulative probability of an episode of hepatic decompensation is 5% at 1 year, and increases to 30% at 10 years from the diagnosis of cirrhosis. Estimated survival rates at 3, 5, and 10 years are 96%, 91%, and 79%. Once hepatic decompensation occurs, however, the 5-year survival rate falls to 50% without liver transplantation.

The recently completed HALT-C study provides more detailed information on the rate of clinical outcomes (death, HCC, ascites, hepatic encephalopathy, variceal hemorrhage, spontaneous peritonitis, and persistent elevation of the Child-Turcotte-Pugh score  $\geq 7$ ) in a cohort of 1,050 subjects in the United States with advanced hepatic fibrosis (Ishak 3 to 6) who were prospectively followed over 3.5 years. Among subjects with cirrhosis at baseline, 28.7% developed a clinical outcome, and among those with bridging fibrosis, 21.5% advanced to cirrhosis over 3.5 years.

Hepatitis C virus infection is one of the most important factors to HCC development; the risk of HCC is 17 times greater in HCV-infected patients compared to HCV-negative individuals. Markers of HCV infection are found in a high proportion of HCC patients in a number of European countries such as France (27% to 58%).

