### 11.4. Sample Size Determination

No formal sample size calculation has been performed. The trial is not designed to evaluate a specific statistical hypothesis but to provide subjects with early access to telaprevir. Therefore, the number of enrolled subjects is not based on statistical but rather practical considerations involving the expected prevalence of HCV infection in the included countries and the projected number of eligible subjects based on major eligibility criteria along with other available therapies. Nonetheless, safety and tolerability data will be summarized using descriptive statistics. The percentage of subjects having selected safety and tolerability events will be estimated and 95% confidence intervals (CIs) for these estimates will be derived. Although no formal statistical hypotheses regarding overall response rates will be tested, the following table provides some guidance on the precision of estimation as measured by the half-width of the derived 95% CIs. For example, if the expected percentage of subjects with a serious adverse event is 10%, the expected 95% confidence interval would be approximately (8.9%, 11.1%) with 3,000 subjects.

| Expected Half-Width of 95% Confidence Intervals for Percentage of Subjects With an Event |                           |              |              |
|-------------------------------------------------------------------------------------------------|---------------------------|--------------|--------------|
| Estimated Event Rate (%)                                                                 | Number of Subjects |              |              |
|                                                                                                 | 2,000              | 3,000 | 4,000 |
| 10                                                                                       | 1.3                       | 1.1          | 0.9          |
| 20                                                                                       | 1.8                       | 1.4          | 1.2          |
| 30                                                                                       | 2.0                       | 1.6          | 1.4          |
| 40                                                                                       | 2.1                       | 1.8          | 1.5          |

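### Section 12.3.2 keeps an undefined class of non-fatal hepatitis C events out of SAE recording unless they are judged associated with telaprevir, contrary to Section 12.3.1, the synopsis and Section 11.5

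*Protocol*

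**What the plan says.** Section 12.3.1 lists what goes into the CRF between the first telaprevir dose and 30 days after the last. One entry is "All serious adverse events, regardless of relationship to telaprevir". The synopsis (Safety Evaluations) carries the same entry. Neither mentions an exception or points to one.

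Section 12.3.2 opens by requiring all SAEs to reach the sponsor within 24 hours. It then narrows this twice:

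- Hospitalization makes an event an SAE, except when it is for "Treatment or care of hepatitis C diseases unless fatal or considered to be related to telaprevir", among other exemptions.
- A separate list is introduced by "program the following occurrences will NOT be recorded or reported as serious adverse events". It includes "Hepatitis C related events, unless fatal or judged to be associated with the use of telaprevir".

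The premise offered is that "Hepatitis C infection is characterized by a series of infections and neoplasms", and the reason is that "Reporting all such events as serious adverse events could divert attention from the serious adverse events that could be related to the study drug". No list of qualifying events is given. Section 12.3.2 also treats the cause of any death within 30 days of the last telaprevir dose as an SAE.

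Section 11.5 says that the events collected and summarized are those defined in Section 12.3.1. Section 11.4 uses the percentage of subjects with an SAE as its worked example of precision.

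**The concern.** The two rules cannot both be followed. A site working from Section 12.3.1 records a non-fatal episode of ascites or variceal bleeding that it considers unrelated to telaprevir. A site working from Section 12.3.2 may leave the same episode out of the SAE data. Because the category is undefined, the reference to infections and neoplasms could also be read to take in serious infection and hepatocellular carcinoma.

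Safety and tolerability are the only data objective here, and the population has severe fibrosis or compensated cirrhosis. Entry requires Child-Pugh Grade A and excludes a history of ascites, encephalopathy or bleeding varices, so an on-study decompensation is a new deterioration. Unchanged pre-existing conditions have their own exemption. The hepatitis C exemption therefore mainly affects new or worsened events.

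Whether such an event counts depends on the investigator's view of causality in an open-label program without a control arm. Section 12.1.2 calls an event unlikely related when another explanation, such as concomitant disease, is more likely. In this population that explanation is always at hand.

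**Working it through.** **Plan's own figure.** Section 11.4 gives a 95% interval of 8.9% to 11.1% for a 10% SAE rate in 3,000 subjects. The half-width is 1.96 × √(0.10 × 0.90 / 3,000) = 0.0107, or 1.07 points, giving 8.93% to 11.07%. The figure reproduces, so the precision arithmetic is not at fault.

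**Direction.** The exemption can only take events out of the Section 12.3.1 count. The recorded percentage is equal to or below the all-cause percentage.

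**Inputs for size.**

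- Window: 12 weeks of telaprevir plus 30 days = 84 + 30 = 114 days; 114 / 365.25 = 0.312 year.
- Lower background rate (Section 1.1): in compensated cirrhosis "the cumulative probability of an episode of hepatic decompensation is 5% at 1 year".
- Higher background rate (Section 1.1): in the cited HALT-C cohort, 28.7% of subjects with cirrhosis had a clinical outcome over 3.5 years.
- Share of subjects with cirrhosis: not given; assumed 25% to 100%.

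**Risk per subject with cirrhosis in the window, constant hazard.**

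- Lower: 1 − (1 − 0.05)^0.312 = 1.59%.
- Higher: 1 − (1 − 0.287)^(0.312 / 3.5) = 2.97%.

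**Largest loss these rates allow.** Assume every such event is serious, non-fatal, judged less than possibly related, and the subject's only SAE. The loss is then share × risk.

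| Assumed cirrhosis share | Loss, percentage points | Subjects of 3,000 | Recorded rate if all-cause is 10% |
|---|---|---|---|
| 25% | 0.40 to 0.74 | 12 to 22 | 9.60% to 9.26% |
| 50% | 0.79 to 1.49 | 24 to 45 | 9.21% to 8.51% |
| 75% | 1.19 to 2.23 | 36 to 67 | 8.81% to 7.77% |
| 100% | 1.59 to 2.97 | 48 to 89 | 8.41% to 7.03% |

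Against the 1.07-point half-width, the loss runs from 0.40 / 1.07 = 0.37 to 2.97 / 1.07 = 2.8 times. The table covers background liver events in cirrhosis only. It counts nothing for subjects with severe fibrosis alone or for infections outside the cited composite.

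**A milder case.** Take a 25% share and the lower rate, and suppose half the events are judged possibly related and so recorded (assumption). About 6 subjects, or 0.2 points, are lost.

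**The case against.** The exemption is deliberate and its reason is given. The hypothesis statement says that only selected safety data are collected, and a footnote to the Time and Events Schedule records SAEs as the protocol describes them, which can be read to include Section 12.3.2. Analyses are descriptive and no comparison with background rates is planned. All of this stands, but it does not reconcile the sections, define the category or tell a reader what the SAE percentage contains.

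Four stronger readings are tempting, and the documents do not support them:

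- *Only events firmly blamed on telaprevir survive.* Section 12.1.1 counts an event as associated if it is possibly related or related. Under Section 12.1.2, possibly related means that causality cannot be excluded. That is a low bar, and a decompensation on triple therapy may well meet it.
- *Deaths disappear.* Fatal events are expressly kept.
- *Exempt events never reach the CRF.* They do if they lead to telaprevir discontinuation or if local regulations require it. A bleed causing anemia leaves an anemia record, and withdrawal reasons are captured. None of these routes restores the SAE count.
- *Up to 89 subjects will be lost.* That needs every assumption in the table to hold at once. The 28.7% composite includes deaths, which are retained, and a persistently raised Child-Turcotte-Pugh score, which need not be serious. A 100% cirrhosis share conflicts with enrolment of subjects with severe fibrosis. Entry criteria exclude prior decompensation and several laboratory markers of advanced disease, and early stopping of telaprevir shortens the window.

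**Conclusion.** The contradiction stands. Section 12.3.2 withholds SAE status from an undefined class of non-fatal events unless they are judged at least possibly related to telaprevir, while Section 12.3.1 and the synopsis require recording regardless of relationship and Section 11.5 relies on Section 12.3.1. The effect on the all-cause SAE percentage is zero or downward and depends on attribution.

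The documents do not fix its size. About 0.4 to 3.0 points is an upper-side illustration that rests on a constant hazard, the full 114-day window, Section 1.1 rates, an assumed cirrhosis share of 25% to 100%, and the worst case for seriousness, attribution and overlap. The true loss is likely smaller and may lie well inside the 1.1-point half-width. The point should be fixed because it acts at data capture, and an event not recorded cannot be reliably recovered at analysis.

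**What to change.** Amend the synopsis and Sections 11.5, 12.3.1 and 12.3.2 to state one rule. Every event in the telaprevir window that meets the seriousness criteria of Section 12.1.1, including non-fatal hepatic decompensation, hepatocellular carcinoma and serious infection, is recorded in the CRF as serious whatever its attribution. Keep the exemptions for unchanged pre-existing conditions and for elective procedures.

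If the sponsor still wants to limit individual SAE reporting of disease-related events, define them by a closed list, record them in the CRF all the same, and report the SAE percentage with and without them. Separate tabulation meets the concern about diverted attention without losing data.

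The cost is a short amendment, some extra forms and a somewhat higher reported SAE percentage.
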